## 1.2 Problem statement

Despite the introduction of ARV therapy, HIV is still a public health problem in Eastern and Southern Africa(1). The wide spread use of the ARV drugs has improved the life expectancy of people living with HIV and/ or AIDS. As a result, there has been an increase in the prevalence of non- AIDS complications such as non- AIDS defining cancers, liver, pulmonary and cardiovascular diseases(2).

The increase in the non – AIDS complications especially the cardiovascular disease risk is linked to platelet and immune activation(18–20,29–31). The ART does not completely abolish the immune activation and the platelet activation(24–27,32) making it a necessity to find additional therapy to the conventional ART therapy, that will decrease the occurrence of these non- AIDS complications and their associated morbidities. ASA promisingly shows to be that additional drug. Therefore, the beneficial effects of ASA in the HIV- infected individuals need to be investigated.

Literature shows that additional therapy to ARV drugs may compromise adherence to ARV drugs among HIV- infected individuals(48). However, when addition of a pill is associated with significant benefit, the addition of a pill or pills may be justifiable. For example, addition of medication for opportunistic infection, methadone maintenance therapy and antidepressants has been reported to improve adherence to ART among HIV- infected patients in some studies(50–52). Therefore, considering the reported benefits of ASA in the HIV- infected population, it is important to study the effect of the addition of ASA on both the HIV disease progression and the adherence to ARV drugs.

### 1.3 Conceptual framework

[figure not shown]

**Figure 1.1: Conceptual Framework**

HIV disease progression is influenced by a range of factors. ART slows HIV disease progression and alters its course significantly, however, for therapeutic success adherence to ART must be nearly perfect to achieve a sustained virologic suppression. Plasma viral load and CD4 cell count are important laboratory measures of the rate of progression. Short term use of ASA is reported beneficial to PLHA as it increases CD4 cell count, decreases plasma viral load and reduces platelet and immune activation. Introducing ASA to the conventional ARV regimen may maximise these benefits without compromising the adherence to ART, which would then lead to reduced morbidity and mortality and hence improved quality of life and survival among PLHA. The proposed study aims at determining the effects of ASA on HIV disease progression among HIV- infected patients initiating ART.

#### **1.4 Rationale**

Since initiation of treatment and care of HIV-infected patients in Tanzania and scaling-up of treatment to reach populations in all settings in the country, parallel efforts have been made to improve compliance to treatment. As observed in the foregone literature review it is prudent to establish the potential benefit of adding ASA in the current ARV treatment regimen in the country and also investigate the impact of adding ASA on treatment adherence. The goal is to establish strategies for enhancing ART impact and further improving treatment outcome. ASA is a cheap drug that is easily available in Tanzania and once its beneficial effect is confirmed its use in ART therapy can be easily implemented in the current National HIV treatment programme.

Findings from this proposed study will provide preliminary data for policy makers especially in the Ministry of Health, Community Development, Gender, Elderly and Children (MoHCDGEC) on the possibility of adding ASA to the conventional ARV treatment in the HIV- infected individuals to reduce morbidity and mortality. Hence, this proposed study will provide preliminary data for future consideration for ASA use in HIV care and treatment.

### 1.5 Research questions

1. What effect does ASA have on HIV viral load among HIV- infected individuals initiating ARV therapy?
2. What effect does ASA have on CD4 counts among HIV- infected individuals initiating ARV therapy?
3. What effect does ASA have on plasma level of immune activation biomarker (sCD14) among HIV- infected individuals initiating ARV therapy?
4. What effect does ASA have on plasma level of platelet activation biomarker (P-selectin) among HIV- infected individuals initiating ARV therapy?
5. What effect does ASA have on T cell activation biomarkers (CD38 and HLA-DR) among HIV- infected individuals initiating ARV therapy?
6. What effect does ASA have on T cell exhaustion biomarker (PD-1) among HIV- infected individuals initiating ARV therapy?
7. What effect does ASA have on morbidity among HIV- infected individuals initiating ARV therapy?
8. What effect does ASA have on all- cause- mortality among HIV- infected individuals initiating ARV therapy?
9. What is the level of adherence to ARV therapy among HIV- infected individuals initiating ARV therapy and ASA or placebo?

## **1.6 Study objectives**

### **1.6.1 Broad objective**

- To determine the effect of low dose of ASA on HIV disease progression and adherence to anti- retroviral therapy among HIV-infected individuals initiating ARV therapy.

### **1.6.2 Primary objective**

The primary objective of the proposed study is:

- To compare the HIV viral loads measured at 2, 3 and 6 months among HIV- infected individuals after initiating ARV therapy alone or ARV therapy and 75mg ASA.

### **1.6.3 Secondary objectives**

The secondary objectives of the proposed study are:

1. To compare the CD4 counts measured at 3 and 6 months among HIV- infected individuals after initiating ARV therapy alone or ARV therapy and 75mg ASA.
2. To compare the plasma levels of immune activation biomarker (sCD14) measured at 3 and 6 months among HIV- infected individuals after initiating ARV therapy alone or ARV therapy and 75mg ASA.
3. To compare the plasma levels of platelet activation biomarker (P- selectin) measured at 3 and 6 months among HIV- infected individuals after initiating ARV therapy alone or ARV therapy and 75mg ASA.
4. To compare percentage of activated T cells (CD38 positive and HLA-DR positive T cells) measured at 3 and 6 months among HIV- infected individuals after initiating ARV therapy alone or ARV therapy and 75mg ASA.
5. To compare percentages of exhausted T cells (PD1 positive T cells) measured at 3 and 6 months among HIV- infected individuals after initiating ARV therapy alone or ARV therapy and 75mg ASA.
6. To compare morbidity among HIV- infected individuals initiating ARV therapy alone or ARV therapy and 75mg ASA.
7. To compare all-cause-mortality among HIV- infected individuals initiating ARV therapy alone or ARV therapy and 75mg ASA.
8. To determine level of adherence to ARV therapy among HIV- infected individuals initiating ARV therapy and ASA or placebo.

### 1.7 Literature review

There are a few studies showing the effect of ASA on HIV disease progression. In one 12- month, three- arm, placebo-controlled pilot study conducted in Zimbabwe investigating the use of ASA in the management of HIV disease, it was shown that 300 mg of ASA given four times a day to ARV naïve HIV- infected patients resulted into no increase in HIV viral load during the follow up period. Unlike in the placebo arm where there was an increase in the HIV viral load(37). In another study also conducted in Zimbabwe but among ARV naïve AIDS patients, there was a decrease in HIV viral load in the first 6 months of a combination of 300 mg ASA four times a day together with chloroquine and micronutrients. When chloroquine was stopped and these patients continued with ASA and micronutrients for an additional 3 months, there was a median HIV viral load decline at the end of 9 months relative to baseline. This decline cannot be ascertained to ASA alone. In the same study however, notwithstanding the net decline some patients' HIV viral load increased(35). Findings from these studies are contradictory and that effects on HIV viral load from the latter cannot be completely ascertained to ASA, it is therefore necessary to conduct further studies to show the effect of ASA on HIV load.

Apart from having effects on the HIV viral load, ASA has also immunologic benefits i.e. it has been observed to increase CD4 count in HIV- infected individuals with or without AIDS. The CD 4 T cells are the primary target cells for the HIV. Therefore, CD4 count reflects the extent of immune depletion and hence it is a direct marker for the risk of morbidity and/ or mortality in HIV- infected individuals. Any agent that can increase the CD4 count is likely to reduce the risk of morbidity and/ or mortality in the HIV- infected population. In a study done in Zimbabwe investigating the use of ASA in the management of HIV disease among ARV naïve patients, it was shown that ASA, in divided doses, of 1.2 grams a day resulted in an increase of CD4 count in a period as short as 24 weeks. However, this increase was followed up by an insignificant drop of the CD4 count at 12 months but still higher than the baseline count (37). In another study, again conducted in Zimbabwe, ARV naïve patients with CD4 counts less than 200 cells/milliliter had their CD4 counts increased within 3 months of 600 mg two times daily use of a combination of ASA and micronutrients. In this study however, it was not possible to ascertain the increased CD4 count to ASA or micronutrients alone (35). In another study done in Nigeria, similarly a combination of ASA and other nutrients resulted into a non-significant increase in CD4 counts

(36). In all these studies however, the sample sizes were small. In the proposed study, a relatively larger sample size of HIV- infected patients initiating ARV therapy is going to be involved.

Literature shows that among other factors, platelet and immune activation have a higher contribution to the increased cardiovascular disease risk in the HIV- infected population(18–20,29–31). Additionally, literature also shows that ARV therapy alone can only partially decrease the exaggerated immune activation and its associated biomarkers in this population(24–27). There is inconsistency in data with regards to the effect of ART to platelet activation and its associated biomarkers. In some reports, levels of platelet activation biomarker normalize to non- HIV- infected levels with ART(27) while in some reports the levels do not decrease(32).

In an effort to find an add-on-therapy to the ARV therapy, studies on effects of ASA on platelet and immune activation have been conducted since ASA is both an antiplatelet and anti-inflammatory drug.

Two studies, both done in the United States (US) by O' Brien M *et al* have shown conflicting findings. In the first study, 81 mg of daily ASA for a week among virologically suppressed HIV- infected individuals on ARV therapy resulted into diminished levels of biomarkers of platelet and monocyte activation ((sP- selectin and sCD14 respectively) and diminished expression of biomarkers of T cell activation(CD38 and HLA-DR ) reflecting a decrease in platelet and immune activation (16). In the other study, however, ASA at doses of 300 mg or 100 mg daily for 12 weeks among ARV therapy- suppressed HIV- infected individuals did not appear to have any effect on the levels of biomarkers of monocyte activation (sCD14) and T cell activation and exhaustion(CD38, HLA-DR, PD-1)(33). Due to this controversy, the proposed study secondarily aims at studying the long- term effects of ASA on platelet activation, monocyte activation and T cell activation and exhaustion and their respective biomarkers (sP- selectin, sCD14, CD38, HLA-DR, PD-1) among HIV- infected individuals initiating ARV therapy in our settings.

In the general population, ASA has been put in chemo preventive uses especially in oncology, cardiovascular medicine and obstetrics to lower the incidences of a number of diseases. Studies have shown that daily ASA reduce the incidence of colorectal cancer and several other cancers and also reduce metastasis therefore lowering the burden of diseases(53). ASA is also used for the primary and secondary prevention of cardiovascular disease. These benefits have been observed in studies involving the general population therefore, may or may not be seen in the HIV

infected individuals and are appreciable after a long-term use of daily ASA. In the HIV- infected population, although data are limited, short term daily use of ASA has been shown to reduce morbidity.

In one study that was conducted among HIV positive ARV naïve men and women with AIDS, who were given ASA (300mg four times daily), micronutrients and chloroquine for six months then switched to ASA (600mg twice a day) and micronutrients for three months, no opportunistic infections were diagnosed during the last three months of the study. Again, in this study there was no evidence of clinical disease progression in any of the patients. On self-report, all but one patient reported improvements in their conditions(35). In another study involving HAART naïve people living with HIV and AIDS, six months of daily ASA use in combination with selenium and multivitamins resulted in improved quality of life which may be due to reduced morbidity(36). In both these studies, a few numbers of patients were involved and also the effects observed cannot be fully ascertained to ASA as it was given together with other drugs or nutrients. The proposed study therefore, will study the effects of ASA singly on morbidity by looking at number of hospital visits for medical attention/ care because of illness and/or number of hospital admissions among HIV infected patients initiating ARV, for six months.

Although data are scarce, daily use of ASA in the HIV- infected population has shown reduction in morbidity(35). Reduced morbidity may indirectly mean reduced mortality. To the best of my knowledge, there are no studies reporting on the effects of ASA on mortality specifically among the HIV- infected population. Many trials conducted looking at the role of ASA in reducing mortality are focused on cardiovascular diseases and involved the general population(54). The proposed study also aims at looking at the effects of low dose ASA on all-cause-mortality in the HIV-infected population.

It is reported that complexity of the ARV regimen has decreased because of the introduction of fixed dose combination ARV drugs therefore improving adherence to the ARV regimens. However, the HIV- infected patients have other prescription drugs, for other comorbid conditions or prophylaxis for opportunistic infections, something which may limit their adherence to ARV drugs. As far as literature could be searched, there are a few studies which have investigated the influence of co medications on adherence to ARV drugs(48,50–52).

In one prospective observational study that involved HIV- patients determining the influence of co medications on ARV therapy adherence, results showed that the non- adherent patients are the ones who had high number of co medications. This may imply that co medication among HIV- patients may compromise their adherence to ARV drugs(48). In other studies however, introduction of co medications such as antidepressants, medications for opportunistic infections and methadone maintenance therapy for intravenous drug users HIV- infected patients resulted into improvement in adherence to ARV drugs(50–52). In the proposed study the level of adherence to ARV therapy among HIV-infected individuals initiating ARV drugs and also taking ASA or placebo is going to be determined.

## 2. METHODOLOGY

### 2.1 Study design

The proposed study will be a phase IIA, double blind, randomized placebo- controlled two sites out- patient based trial with two treatment groups.

### 2.2 Study design diagram

[figure not shown]

**Figure 2.2: Study design flow chart.**

### 2.3 Study population

Newly recruited HIV infected patients initiating ART attending CTCs in Dar es Salaam.

### 2.4 Number of Subjects.

The study will involve 454 newly recruited HIV infected patients initiating ART attending CTCs in Dar es Salaam who will be equally obtained from each of the two study sites.

### 2.5 Expected duration of study population

The proposed study is expected to run for 1 year, from start of subject screening to last subject finishing the study. The recruitment period will be six months and each individual

subject will be on study treatment for six months and will also be followed- up for six months.

## **2.6 Study Area**

The proposed study will be conducted in Dar es Salaam which is the largest city in the United Republic of Tanzania. According to the 2012 official census, Dar es Salaam had a population of 4,364,541. Between October 2016 and August 2017, the prevalence of HIV-infection in the region was 4.7% (55). Administratively, Dar es Salaam is divided into five districts namely Ilala, Kinondoni, Temke, Kigamboni and Ubungo. Within the five districts there are a total of 269 HIV Care and Treatment Centres (CTCs), 235 of them are supported by Management and Development for Health (MDH), and the rest are supported by programs or organizations like Pastoral Activities and Services for People with AIDS Dar es Salaam Archdiocese (PASADA), PharmAccess International (PAI) and John Snow, Inc. (JSI). The cumulative number of persons ever enrolled in care by the end of September 2017 was 317923 persons. On a daily basis, on average 3-5 patients, 1-2 patients and 1 or no patient are newly diagnosed with HIV infection at big, medium and small CTCs, respectively. These clinics operate on six days of a week where Fridays and Saturdays are for paediatric patients and adolescents, respectively, and patients are seen monthly. We propose to conduct the study at the public HIV clinics supported by MDH in Dar es Salaam which include Mbagala Rangi Tatu and **Mwananyamala**. This selection of the study sites is based on the high enrolment of patients and although these clinics are situated in different facilities, they are run similarly.

## **2.7 Primary and Secondary Outcome Measures**

The primary outcome of interest will be virological response. The main virological outcome that will be observed will be the proportion of patients in different arms reaching viral loads of < 50 copies/ millilitre at months 2, 3 and 6 (indicating viral suppression) and > 1000 copies/ millilitre at month 6 (indicating virologic failure).

The secondary outcomes will be immunologic response measured by CD4 count and clinical responses measured by morbidity and death from any cause. With the use of ART alone there is an increment of 30% at 3 months in CD4 count from baseline value(56). With the addition of ASA to the ART, it is expected that the CD4 count will rise by > 30% from baseline value at months 3. Other secondary outcome measures will be plasma levels of sCD14 and sP- selectin, percentage

of activated T cells (CD38 positive and HLA-DR positive T cells), percentage of exhausted T-cells (PD-1 positive T cells), percentage adherence to ART and compliance to study medications, adverse events. The levels of sCD14 and sP- selection are expected to drop to those of non- HIV infected population by 6 months(16).

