**Materials and Methods:** The study will be a phase IIA randomized double blind, placebo-controlled trial with two study groups involving 454 antiretroviral drugs naïve adult patients initiating ART who are attending HIV clinics at **Mwananyamala** and Mbagala Rangi Tatu in Dar es Salaam. Patients in the two study groups will be receiving, in addition to ARV drugs, 75 mg ASA or placebo once daily for six months. They will be followed up monthly for a period of six months. Blood samples will be collected at baseline for all the tests and at months 6 for lipid profile, full blood picture (FBP), renal function test (RFT) and liver function test (LFT), at

months 3 and 6 for CD4 count, at months 2, 3 and 6 for HIV viral load and at months 3 and 6 for plasma levels of soluble CD14 (sCD14), soluble P- selectin (sP- selectin) and for markers of T cell activation and exhaustion. Urine will be collected to exclude pregnant women. The primary outcome will be virological response i.e. the proportion of patients in the two arms reaching viral loads of < 50 copies/ millilitre at months 2, 3 and 6 (indicating viral suppression) and > 1000 copies/ millilitre at month 6 (indicating virologic failure). The secondary outcomes will be immunologic response measured by CD4 count and clinical responses measured by morbidity and death from any cause. Other secondary outcome measures will be plasma levels of sCD14 and sP- selectin, percentage of activated T cells (CD38 positive and HLA-DR positive T cells), percentage of exhausted T-cells (PD-1 positive T cells), percentage adherence to ART and compliance to study medications, adverse events. Data will be analysed by intention to treat. The study outcomes in the two treatment groups will be compared using Chi- square, Fisher's exact or student's t tests and descriptive statistics will be used where appropriate.

**Budget of the study;** The estimated budget for the proposed study 123,722,026.40 Tshs

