## **2.13 Statistical Methods**

### **2.13.1 Sample Size estimation**

The required sample size is 227 participants in each treatment arm making a total of 454 participants.

Assuming that the proportion of patients with < 50 copies/ml at 8 weeks in the control group (ARV alone) is 75%(60), then 227 patients will be required, in each study treatment group, if a relative risk for the ARV + ASA treatment group is 1.15, assuming loss to follow up of 10%, a power of 80% and a significance level of 0.05.

| Item                                                                                                | Value                                     |
|------------------------------------------------------------------------------------------------------------|--------------------------------------------------|
| Proportion of patients with < 50 copies/mL at week 8 after ART initiation in the control group (ARV alone) | 75%                                              |
| Relative risk =1.15 for intervention group(ARV + ASA)                                                      | 1.15 (i.e. 86% in intervention group(ARV + ASA)) |
| Expected loss to follow up                                                                                 | 10%                                              |
| Significance level for a two-sided test                                                                    | 0.05                                             |
| Power                                                                                                      | 80%                                              |
| Total patients in each group                                                                               | 227                                              |

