### **2.13.3 Statistical Analysis Plan**

The data will be double entered into a computer by two different data entry clerks and the entered data will then be verified and cleaned before being subjected to analysis using the SPSS statistical program. Intention to treat analysis will be done.

Chi- square or Fisher's exact test will be used for comparison of proportions and Student's t test for comparison of means between the two treatment groups.

Descriptive statistics will also be used where appropriate. A two tailed P-value of  $<0.05$  will be considered significant.

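### Four virological comparisons share primary status at an unadjusted 0.05 with no lead comparison or success rule, and only suppression at week 8 was sized

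*Protocol*

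**What the plan says.** - **Primary outcome (2.7 and the abstract).** Section 2.7 counts patients "reaching viral loads of < 50 copies/ millilitre at months 2, 3 and 6 (indicating viral suppression) and > 1000 copies/ millilitre" at month 6. The abstract agrees: "The primary outcome will be virological response i.e. the proportion of patients in the two arms reaching viral loads of < 50 copies/ millilitre", at the same three visits, together with the same failure measure.
- **Primary objective (1.6.2).** "To compare the HIV viral loads measured at 2, 3 and 6 months among HIV- infected individuals". No visit is given precedence.
- **Analysis (2.13.3).** "Chi- square or Fisher's exact test will be used for comparison of proportions", and a two-tailed P-value below 0.05 "will be considered significant". There is no testing order, division of alpha, or rule on how many primary comparisons must succeed.
- **Sample size (2.13.1).** "Assuming that the proportion of patients with < 50 copies/ml at 8 weeks in the control group (ARV alone) is 75%(60"; the relative risk is "1.15 (i.e. 86% in intervention group(ARV + ASA". The inputs are a two-sided 0.05, 80% power and 10% loss to follow-up, giving 227 per arm. No rate or effect is given for suppression at month 3 or 6, or for failure at month 6.

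**The concern.** The sample size belongs to a trial with one primary test, whereas the outcome section describes a trial with four. Without a rule linking them, the comparison that decides the trial can be chosen after the results are known. One of the two planning figures then fails:

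- If a significant result on any of the four is enough, 0.05 is the level of each test and not the error rate of the primary question.
- If all four are needed, the error rate is safe, but 80% is the power of one component only.

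The protocol does not say which applies, so a reader of the eventual result could not tell what error rate or power lay behind it.

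**Working it through.** **1. Reproduce the stated sample size (week 8 only).** From 2.13.1: p1 = 0.75, p2 = 0.86, two-sided alpha 0.05 (z = 1.960), power 0.80 (z = 0.842), 10% loss. The mean proportion is 0.805.

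n = [1.960 × √(2 × 0.805 × 0.195) + 0.842 × √(0.75 × 0.25 + 0.86 × 0.14)]² / 0.11²

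n = [1.098 + 0.467]² / 0.0121 ≈ 203 evaluable per arm

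203 / 0.90 = 226 per arm, against 227 stated. The plan's figure holds for this single comparison.

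**2. Power at the planned size.** 227 × 0.90 ≈ 204 evaluable per arm. Power = Φ[(0.11 × √204 − 1.098) / 0.555] = Φ(0.852) = 80.3%.

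**3. Error rate if any one of four suffices.** Under independence, 1 − 0.95⁴ = 18.5%. The tests are not independent, because the same patients are measured repeatedly and nobody can be both suppressed and failing at month 6. I simulated four two-sided z-tests under no treatment effect (1,000,000 draws), with the failure test negatively correlated with the suppression tests. The correlations are assumed:

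| Correlation between test statistics | At least one of four significant | At least one of the three suppression tests |
|---|---|---|
| 0 | 18.6% | 14.3% |
| 0.3 | 17.4% | 13.6% |
| 0.5 | 15.6% | 12.6% |
| 0.7 | 13.0% | 10.9% |
| 0.9 | 9.4% | 8.4% |

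These count false positives in either direction, as a two-sided 0.05 does. Counting only results that favour aspirin, the four-test figure runs from 9.6% (correlation 0) to 4.7% (correlation 0.9), against a nominal 2.5%.

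A second simulation used patient-level data with assumed suppression of 75%, 82% and 88%, assumed failure of 6%, 204 per arm and uncorrected chi-square tests. It gave 17.3% to 13.5% for correlations of 0 to 0.9 on the underlying scale. That scale differs from the table's: a correlation of 0.9 there gives only about 0.6 to 0.7 between the suppression tests. With continuity correction, runs under similar assumptions gave about 10% to 13%.

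**4. Power if all four must succeed.** Joint power cannot exceed that of the weakest component. Month 2 alone caps it at 80.3%, and any further requirement can only lower it. As an illustration with assumed failure rates and 204 per arm, halving month-6 failure from 10% to 5% has about 48% power, and from 5% to 2.5% about 26%.

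**5. Two ways to repair it.**

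| Option | Alpha for month 2 | Evaluable per arm | Randomised per arm |
|---|---|---|---|
| Month 2 as sole primary | 0.05 | 203 | 226 (227 stands) |
| Four alternative primaries, Bonferroni | 0.05 / 4 = 0.0125 | 288 | 320 (640 in total) |

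If the second option kept the planned 204 evaluable per arm, power for month 2 would fall from 80.3% to 62.1%.

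**The case against.** **The 5% is not stated as a trial-wide rate.** Sections 2.13.1 and 2.13.3 give 0.05 as the level of a test, and nowhere say that any single success makes the trial positive. This stands. A reader might infer that the error rate is inflated as a matter of fact, but the documents support that only under an any-one-suffices rule, which they do not state.

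**A lead comparison can be guessed.** Alpha, power and N are tied to week 8 and to nothing else, and sizing on one visit of a repeated measure is common practice. This softens the point. It does not answer it, because 1.6.2, 2.7 and the abstract give month 2 no precedence.

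**An analysis plan may adjust for multiplicity, and this is a phase IIA trial meant to give preliminary data.** Both are fair. But which endpoint is primary is a protocol decision. This protocol has made it, and has set an unadjusted significance rule beside it.

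**Two further criticisms that a reader might infer are not supported.**

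- A relative risk of 1.15 cannot occur where control suppression is 87% or more (1 / 1.15 = 0.870). The arithmetic is right, but the protocol plans that effect only at week 8 with a 75% control rate, and gives no control rate for later visits.
- Section 1.6.2 speaks of comparing viral loads, which might suggest a further primary contrast on the values themselves. It is objective-level wording that 2.7 turns into proportions, and no such analysis is written.

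**Conclusion.** The point holds as a missing lead comparison and decision rule. The primary outcome contains four comparisons, each judged at 0.05, while the design figures belong to one of them. If any one suffices, the chance of a false-positive primary result is roughly 9% to 17%, with 18.5% as the independence value. The range rests on assumed correlations and event rates and on the choice of test, but every scenario examined exceeds 5%. If all four must succeed, error is not inflated, but the stated 80% power does not apply. The sample size is not wrong for the comparison it was built on.

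**What to change.** In 1.6.2, 2.7 and the abstract, name the proportion below 50 copies/ml at month 2 (week 8) as the single primary endpoint, tested at two-sided 0.05. Make suppression at months 3 and 6 and failure at month 6 secondary. Either report them with 95% confidence intervals and no stand-alone significance claim, or test them in a stated fixed order only if month 2 succeeds. The fixed order also holds the 5% at the same sample size and still allows formal claims at later visits, although those comparisons remain unsized.

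Month 2 is the natural choice. It is the sized comparison, and its blood is drawn for the study (2.10) and tested at the central laboratory (2.11.6). Month-6 results are traced from patient records (2.10), come from site laboratories (2.11.6), and may be missing, as 2.16 acknowledges.

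Cost: no extra patients, and 227 per arm stands. The change affects scientific intent, so under 2.15.3 it is an amendment needing ethics committee approval, and it should be made before treatment codes are opened. The scientific price is that the end-of-treatment and failure results lose primary status, so a difference seen only at a later visit cannot be claimed as the primary result.
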